# Flexible ureteroscopy with a flexible and navigable suction ureteral access sheath versus mini‐percutaneous nephrolithotomy for 1–2 cm lower pole renal stones: Protocol for an international, multicentre, randomized non‐inferiority trial (FLAME trial)

**DOI:** 10.1002/bco2.70114

**Published:** 2025-11-29

**Keywords:** FANS, flexible and navigable suction ureteral access sheath, flexible ureteroscopy, lower pole, PCNL, renal stones

## Abstract

**Background:**

Lower pole renal stones measuring 1–2 cm remain challenging to treat. While mini‐percutaneous nephrolithotomy (mini‐PCNL) provides high stone‐free rates (SFRs), it carries tract‐related morbidity. Flexible ureteroscopy (f‐URS) is less invasive but limited in SFR. The flexible and navigable suction ureteral access sheath (FANS) has shown promise in improving stone evacuation and intrarenal pressure control. We hypothesize that FANS f‐URS is non‐inferior to mini‐PCNL for patients with 1–2 cm lower pole stones in SFR.

**Study Design:**

The FLAME trial is an international, multicentre, randomized, non‐inferiority study directly comparing FANS‐f‐URS with mini‐PCNL in this setting.

**Endpoints:**

The primary outcome is immediate SFR within 72 hours on low‐dose CT. Secondary outcomes include SFR at 1 month, operative time, postoperative pain, hospital stay, complications (Clavien–Dindo) and quality‐of‐life changes.

**Patients and Methods:**

A total of 640 adults with CT‐confirmed 1–2 cm lower pole renal stones will be randomized 1:1 to undergo FANS‐f‐URS or mini‐PCNL across 20 high‐volume urology centres worldwide. Randomization is centralized and stratified by site. Radiologists and statisticians will remain blinded to allocation. Sample size was calculated assuming an 85% SFR for both arms, an 8.5% non‐inferiority margin, 80% power and 15% attrition. Analyses will follow both intention‐to‐treat and per‐protocol principles.

**Trial registration:**

ClinicalTrials.gov NCT07159035.

## BACKGROUND

1

Lower pole renal stones measuring 1–2 cm pose a unique endoscopic challenge, as there is currently no clear indication or contraindication favouring one treatment modality over the other. The latest European Association of Urology guidelines^1^ advise that, in the presence of unfavourable lower pole anatomy, “endourology” should be the first‐line approach. However, it is unclear whether flexible ureteroscopy (f‐URS) or percutaneous nephrolithotomy (PCNL) is preferred. Mini‐PCNL achieves high stone‐free rates (SFRs) but carries a greater risk of bleeding and tract‐related morbidity.^2^ In contrast, conventional f‐URS offers a minimally invasive alternative yet often results in lower SFRs in the dependent lower calyx due to difficult deflection angles, resulting in suboptimal access and fragment evacuation.^3^, ^4^

In recent years, f‐URS technology has made monumental advances. The advent of the flexible and navigable suction ureteral access sheath (FANS) and enhanced single‐use digital ureteroscope deflection mechanics allows navigation of the FANS and ureteroscope tip into target calyces that were previously challenging to reach, mitigating the traditional disadvantages of retrograde access.^5^ Current FANS and flexible ureteroscope technology have brought about active fragment evacuation, markedly enhanced intraoperative visibility, reducing intrarenal pressure and facilitating complete stone clearance in the current suction endourology era.^6^, ^7^

Given these technological improvements, several observational studies have reported favourable outcomes for FANS f‐URS in managing lower pole stones.^4^, ^8^ Currently, there is still a paucity of high‐level evidence to determine whether FANS f‐URS can achieve comparable efficacy to mini‐PCNL. With the aim of addressing this evidence gap and potentially expanding the armamentarium for intermediate‐sized renal calculi, we have designed an international, multicentre, randomized non‐inferiority trial comparing FANS f‐URS with mini‐PCNL in this challenging cohort. This study is titled the FLAME trial, an acronym for: Flexible ureteroscopy for Lower pole stones And Mini pErcutaneous nephrolithotomy.

## STUDY DESIGN

2

The aim of this international, multicentre, randomized non‐inferiority trial is to determine whether FANS f‐URS is non‐inferior to mini‐PCNL in terms of SFR for 1–2 cm lower pole renal stones. The primary research question is whether FANS f‐URS achieves SFRs comparable to those of mini‐PCNL, and secondary objectives include comparing perioperative safety (complication rates), operative time, hospital stay duration, patient‐reported pain and recovery metrics and overall health‐related quality of life after each procedure. By evaluating both efficacy and patient‐reported outcomes, this study seeks to inform best practices for managing intermediate‐sized lower‐pole stones.

## ENDPOINTS

3

### Primary outcome

3.1

**Immediately stone‐free rate (SFR)**: no residual stone or stone fragments larger than 2 mm on CT scans within postoperative 72 hours is defined as stone‐free.

Residual fragments (RFs) were classified based on the bone window of CT imaging as follows:Grade A: 100% stone‐free/zero fragment rate (ZFR).Grade B: Single RF < 2 mm.Grade C: Single RF measuring 2–4 mm.Grade D: Single or multiple RF > 4 mm.

For this study, Grades A and B patients were considered stone‐free, requiring no additional imaging. Patients classified as Grades C and D were categorized as non‐stone‐free. This definition aligns with contemporary endourology trial standards.

### Secondary outcomes

3.2

**Final SFR**: SFR at 1 month based on low‐dose CT scan. No residual stone, or no stone fragments larger than 2 mm under CT scan are defined as stone‐free.
**Operative time**: For the FANS f‐URS group, the operative time is characterized as the duration from the insertion of the endoscope into the urethra to the completion of stent placement. For the mini‐PCNL group, the operation time is defined as from retrograde placement of the ureteric catheter to the placement of nephrostomy tubing or removal of percutaneous access.
*
**Postoperative pain levels:** assessed within 24 hours using a 10‐point visual analogue scale (VAS)*.^9^

**Duration of hospital stay**: *Calculated from day of surgery to day of discharge, rounded up to the nearest whole day*.
**Complications:** All adverse events occurring within 1 month post‐procedure, graded by the Clavien–Dindo classification.^10^

**Improvement of Quality‐of‐Life Score**: *Measured preoperatively and at 1 month using the Wisconsin Stone Quality of Life questionnaire*.^14^, ^16^

## ELIGIBILITY CRITERIA

4

Inclusion criteriaAdults aged 18–75 years;American Society of Anesthesiology (ASA) score 1–3;Lower pole renal stones—single or multiple—with a maximal diameter of 1–2 cm confirmed by CT;Ability to provide written informed consent and adhere to trial requirements.

Exclusion CriteriaSignificant urinary tract anatomical anomalies (e.g. horseshoe kidney, ileal conduit);Stones located within a calyceal diverticulum;History of open nephrolithotomy or ureterolithomy (due to resultant intrarenal anatomical distortion);Absolute contraindications to either FANS‐f‐URS or mini‐PCNL, including:Uncorrectable coagulopathy;Active, uncontrolled urinary tract infection;Severe cardiopulmonary disease precluding safe general anaesthesia (e.g. decompensated heart failure, refractory COPD);Pregnancy;Inability to tolerate lithotomy or prone positioning;
Inability to understand or complete trial documentation.

## METHODS AND ANALYSIS

5

### Study overview

5.1

This is a multicentre, prospective, non‐inferiority, randomized controlled trial. The study will be conducted in accordance with the Declaration of Helsinki and the International Conference on Harmonization – Good Clinical Practice (ICH‐GCP).^11^

### Patient and public involvement

5.2

Two patient representatives reviewed the consent form and provided feedback on language clarity. There is no other direct patient involvement in trial design.

### Setting

5.3

This international trial will be conducted at 20 high‐volume urology centres—17 in China, one in the Russian Federation, one in India, and one in Turkey—each with established expertise in renal stone management. Each participating site performs a minimum of 300 FANS f‐URS and 200 mini‐PCNL procedures annually, ensuring both proficiency and timely patient enrolment.

### Identification and enrolment of potential participants

5.4

Procedures for identifying and consenting participants will be tailored to each centre's local practices and patients' needs. Clinicians or trained research staff will screen all patients presenting with suspected renal stones during routine workflow. A detailed screening log will record every assessed patient and the reason for exclusion (e.g., ineligibility, refusal), to populate the CONSORT flow diagram.

When a 1–2 cm lower pole stone is confirmed by CT and all eligibility criteria are met, patients will receive an information leaflet describing the trial's purpose, procedures, potential benefits and risks of FANS f‐URS versus mini‐PCNL. They may discuss any questions with the local clinical team and consent during either their outpatient appointment or inpatient stay. Written informed consent will be obtained prior to any study‐specific procedures; those unable or unwilling to consent will be excluded. Upon receiving the participant's permission, their urologist will be informed of trial enrolment. Once consent and baseline assessments are completed, participants will be randomized to the FANS f‐URS or mini‐PCNL arm.

### Randomization and allocation

5.5

Participants at respective institutions will be randomized in a 1:1 ratio to either the FANS f‐URS or mini‐PCNL arm, with each site enrolling 32 patients. Randomization will be performed centrally via a secure web‐based system at the time of enrolment, using computer‐generated permuted‐block sequences of varying sizes to maintain allocation concealment. Stratification by centre ensures balance across sites, and block sizes will be kept confidential. Investigators will obtain treatment assignments directly from the web application only after the patient's eligibility and consent have been confirmed.

### Intervention

5.6

Two endourological approaches will be evaluated in this trial: (1) FANS f‐URS and (2) mini‐PCNL. Both interventions will follow the standardized protocols described in Section 5.7 to ensure consistency across all sites.

### Operation protocol

5.7

A standardized operating methodology, approved by the principal investigator at each centre, will be implemented to ensure consistency across sites. Monthly monitoring visits will be conducted to verify adherence to the protocol and address any procedural deviations.

All patients will undergo non‐contrast CT and intravenous pyelogram preoperatively to confirm stone location and measure stone diameter, area and volume, as well as to assess the infundibulopelvic (IP) angle and infundibular length and width.^12^ Stone burden and density will be quantified using the same validated software at each centre. Standard perioperative antibiotic prophylaxis—either cefuroxime 1500 mg or levofloxacin 500 mg—will be administered 30 minutes before the procedure. Patients with a positive preoperative urine culture will receive tailored antibiotic therapy for 5–7 days based on sensitivity results prior to surgery.

#### Endoscopic procedure

5.7.1

#### FANS f‐URS

5.7.2

The procedure will be performed under general anaesthesia with the patient in the lithotomy position. A 5 Fr open‐ended ureteral catheter will be inserted into the ureter, followed by retrograde pyelography to evaluate the upper urinary tract. A 0.035/0.038‐in. guidewire will then be advanced into the renal pelvis. Depending on the patient's anatomy, ureteral condition and device availability, the surgeon will select a FANS‐sized 12/14 Fr, 11/13 Fr or 10/12 Fr. If even the smallest 10/12 Fr sheath cannot be advanced, a 6 Fr double‐J stent will be placed and the procedure scheduled two weeks later as staged f‐URS. All FANS f‐URS procedures will be performed using a 7.5 Fr single‐use digital flexible ureteroscope. Stones are fragmented using either a Holmium:YAG or Thulium fibre laser (≤30 W, 200 μm fibre), with continuous irrigation (50–150 ml/min) and suction (80–120 mmHg). Stone relocation will be allowed at the surgeon's discretion using baskets or other auxiliary tools if judged necessary for optimal stone clearance. Upon conclusion of the procedure, ureteral injuries will be visually assessed and classified according to the Traxer and Thomas endoscopic classification of ureteric injury,^13^ then both the FANS and scope will be withdrawn. A 6 Fr double‐J stent is placed for two weeks based on ureteral condition; routine Foley catheter placement is omitted.

#### Mini‐PCNL

5.7.3

Under general anaesthesia, a 5 Fr ureteral catheter is placed cystoscopically and a 16 Fr Foley catheter is inserted for bladder drainage. For supine mini‐PCNL, the patient remains in the supine (Galdakao‐modified Valdivia) position; for prone mini‐PCNL, they are repositioned to prone following catheter placement. Percutaneous access will be achieved using an 18‐gauge coaxial needle to puncture the desired calyx under fluoroscopic or ultrasound guidance. Tract dilatation will be accomplished using fascial dilators up to 20 Fr. When multiple nephrostomy tracts are necessary to remove the stones, the same technique will be employed for each tract. Endoscopic combined intrarenal surgery (ECIRS) will not be allowed in this trial, to maintain protocol consistency and avoid confounding effects. Fragmentation of the stone burden will be accomplished using either a pneumatic lithotripter, Holmium:YAG or Thulium fibre laser. At the end of the procedure, a 6 Fr double‐J ureteral stent will be left in place. The decision to place a nephrostomy tube is made at the operating surgeon's discretion. Tubeless mPCNL will be selectively performed in patients who meet the following criteria: absence of significant residual stones, no visible perforations, no significant bleeding and no anticipated need for second‐session procedures.

### Follow‐up and data collection

5.8

A low‐dose, non‐contrast CT scan with 2‐mm slices will be obtained within 72 hours post‐procedure to assess immediate stone‐free status, defined as no visible stones or only fragments ≤ 2 mm in the bone window. Routine blood tests and serum procalcitonin will be drawn within two hours of surgery to screen for infection, and haemoglobin will be compared between preoperative and two hours postoperative samples; any patient with a haemoglobin below 70 g/l will receive a blood transfusion.

In the FANS f‐URS group, patients with no significant discomfort may be discharged within 24 hours of surgery. In the mini‐PCNL group, if a nephrostomy tube was placed, it will be removed 1–3 days after the effluent becomes grossly clear, followed by patient discharge. All patients will have their 6 Fr double‐J stents removed at two weeks. Health‐related quality of life will be measured using the standardized Wisconsin Stone QoL questionnaire before surgery and again at one month.^14^ Stone composition will be analysed by infrared spectroscopy using a uniform methodology at each centre. At one month, a follow‐up low‐dose non‐contrast CT will be performed only in patients with residual fragments on the 72‐hour scan; those rendered stone‐free at 72 hours will not undergo further imaging.

Patients' characteristics and clinical outcomes will be recorded on a pre‐established case report form (CRFs). Stone size will be defined as the largest diameter of the stone. For multiple stones, the stone size will be defined as the cumulative sum of the maximal diameters of all stones. Grading of hydronephrosis will be evaluated according to the Onen hydronephrosis grading system.^15^ For the FANS f‐URS group, the operative time is characterized as the duration from the insertion of the endoscope per urethral to the completion of stent placement. For the mini‐PCNL group, the operation time is defined as from retrograde placement of ureteric catheter to the placement of nephrostomy tubing or removal of percutaneous access. Hospital stay will be rounded up to the nearest whole day and calculated from the day of surgery to the day of discharge.

Each recruited patient will have three CRFs completed by the research team at the recruiting site. A baseline CRF will be completed at the time of randomization. A treatment CRF will be completed following the randomized intervention (operation). The CRFs at 1‐month post‐operation will be completed and entered on‐site by the centre coordinators at the recruiting centres. Data on any additional interventions received and complications will be documented. Table 1 shows the schedule of outcome assessment and data collection.

**TABLE 1 bco270114-tbl-0001:** Schedule of enrolment, interventions and assessments.

Trial period	Screening (−4 wk to 0)	Allocation (0)	Post‐allocation	Close‑out (1 mo)
	Timepoint: −t1	Timepoint: 0	Timepoints: t1 = 72 h; t2 = 2 wk	Timepoint: t3 = 1 mo
ENROLMENT				
Eligibility screen	X			
Informed consent	X			
Preoperative CT & baseline labs	X			
Wisconsin Stone QoL (baseline)	X			
RANDOMIZATION & ALLOCATION				
Randomization via web system		X		
INTERVENTIONS				
FANS fURS or mini‑PCNL procedure		X		
ASSESSMENTS				
Immediate post‑op labs (Hb, PCT)			X	
Non‑contrast CT (2 mm slices)			X	
Pain VAS (24 h)			X	
Hospital stay (days)			X	
Double‑J stent removal			X	
Wisconsin Stone QoL (follow‑up)				X
Low‑dose CT if residual within 72 h				X
Complications (Clavien–Dindo grading)			X	X
Stone analysis (infrared spectra)			X	

QoL – quality of life; FANS‐fURS – flexible and navigable suction ureteral access sheath flexible ureteroscopy; mini‐PCNL – mini‐percutaneous nephrolithotomy; Hb – haemoglobin; PCT – procalcitonin; CT – computed tomography; VAS – visual analogue scale.

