### Sample size

5.11

Based on published literature, the immediate SFR for mini‐PCNL in 1–2 cm lower pole stones is approximately 85%; we therefore assume an immediate SFR of 85% for both the mini‐PCNL and FANS f‐URS arms^8^, ^17^, ^18^. A non‐inferiority margin of 8.5% has been selected, as an absolute reduction in SFR of up to 8.5% is deemed the maximum clinically acceptable loss of efficacy given the benefits of FANS f‐URS (less invasiveness, faster recovery and lower bleeding risk) and aligns with margins used in similar endourological trials.^8^ Using simulations conducted in Stata with an 80% power and an alpha level of 2.5%, the required sample size is 278 participants per group (totalling 556). To account for an anticipated 15% loss to follow‐up or withdrawal, we inflate each arm to 320 participants, yielding a final enrolment target of 640 patients.

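### Lower bleeding risk helps justify the 8.5-point margin, but no bleeding outcome is named and the only scheduled quantitative measure is haemoglobin at two hours

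*Protocol article*

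**What the plan says.** Section 5.11 (Sample size) states that a non-"inferiority margin of 8.5% has been selected" and defends it by the benefits expected of FANS f-URS: "less invasiveness, faster recovery and lower bleeding risk". The Background also names bleeding as a drawback of mini-PCNL.

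Section 3.2 lists six secondary outcomes: final stone-free rate, operative time, pain, hospital stay, complications and quality of life. Haemoglobin change, transfusion and bleeding are not named. The complications outcome is broad: "All adverse events occurring within 1 month" after the procedure, graded by Clavien–Dindo. Section 5.8 and Table 1 add that further interventions are recorded and that complications are assessed both after allocation and at 1 month.

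For haemoglobin, section 5.8 says that "haemoglobin will be compared between preoperative and two hours postoperative samples". Table 1 has one matching row, for immediate postoperative labs, and no later sample is scheduled. In the same section, a nephrostomy tube, where one was placed, comes out 1–3 "days after the effluent becomes grossly clear". Section 5.7.3 allows tubeless mini-PCNL only in selected patients, and absence of significant bleeding is one of the criteria. FANS patients without significant discomfort may go home within 24 hours.

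Section 5.12 compares continuous outcomes by an unadjusted t-test or Mann–Whitney test.

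**The concern.** When a margin is defended as a trade, the trial should be able to show whether the benefits on the other side of the trade arrived. Faster recovery has named measures here (hospital stay, pain, quality of life). Lower bleeding risk has none. It is visible in two places only: mixed with infection, ureteral injury and everything else in the pooled complications, and in one early haemoglobin comparison that is described under data collection but not listed as an outcome.

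The timing adds a second, softer problem. If blood loss continues after two hours in some mini-PCNL patients, the sample records only part of the difference between arms. The Discussion ties adoption of FANS f-URS to non-inferiority plus clear advantages in safety, recovery or patient-reported outcomes, so a poorly measured bleeding benefit would weaken the safety part of that reading. An analysis plan can define how haemoglobin is analysed. It cannot supply a sample that was never scheduled.

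**Working it through.** **1. The plan's own figure.** Inputs from section 5.11: "we therefore assume an immediate SFR of 85% for both the" arms, margin 0.085, and simulations "with an 80% power and an alpha level of 2.5"%, read as one-sided. With unpooled variance,

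n = (1.96 + 0.8416)² × 2 × 0.85 × 0.15 / 0.085² = 277.02, rounded up to 278.

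This matches the article: "the required sample size is 278 participants per group". No bleeding quantity enters the formula, so naming or re-timing a bleeding measure changes neither the margin nor the sample size.

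**2. What captures bleeding.**

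| Source | Captures | Limit |
|---|---|---|
| Complications, section 3.2 | Bleeding events, transfusions and re-interventions to 1 month | Pooled with all other complications |
| Haemoglobin, section 5.8 | Quantitative fall in every patient | One sample, at two hours; not a listed outcome |

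**3. What the timing implies.** Section 5.8 allows for effluent that is not yet clear, and keeps the tube in for 1–3 days after it clears. Section 5.7.3 makes no significant bleeding a condition of going tubeless, so patients who bleed significantly would be expected to have a tube. They are the patients in whom a two-hour value is most likely to be incomplete, and under the assigned treatment they are in the mini-PCNL arm. It follows that later loss may be missed, plausibly more in that arm. If so, the measured difference is too small, which works against FANS f-URS.

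**4. Illustrative size.** The documents give no transfusion rate, haemoglobin SD, expected difference or share of loss visible at two hours. Every input below is therefore an assumption, apart from the number per arm: 320 × 0.85 = 272 after the stated 15% attrition, or 320 with no loss.

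*Transfusion*, Fisher's exact test, two-sided 5%, 272 per arm:

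| Assumed rates | Expected events | Power |
|---|---|---|
| 1% vs 0% | 2.7 vs 0 | 6% |
| 2% vs 0.5% | 5.4 vs 1.4 | 19% |
| 3% vs 1% | 8.2 vs 2.7 | 27% |
| 3% vs 0.5% | 8.2 vs 1.4 | 50% |

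*Haemoglobin*, difference detectable with 80% power = (1.96 + 0.84) × SD × √(2/272). For SD 8, 10, 12 and 15 g/l this is 1.9, 2.4, 2.9 and 3.6 g/l.

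*Incomplete capture.* Take SD 12 g/l and a true difference of 5 g/l. The standard error is 12 × √(2/272) = 1.03 g/l with 272 per arm and 12 × √(2/320) = 0.95 g/l with 320. Power = Φ(difference / SE − 1.96):

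| Share visible at two hours | Difference seen | Power, 272 per arm | Power, 320 per arm |
|---|---|---|---|
| 100% | 5.0 g/l | 99.8% | above 99.9% |
| 70% | 3.5 g/l | 93% | 96% |
| 50% | 2.5 g/l | 68% | 75% |

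Under these assumptions haemoglobin is much the more informative bleeding measure, and an early sample costs some power but does not make the comparison useless. Little follow-up loss is likely two hours after surgery, so the 320 column is probably nearer for the sample as now scheduled.

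**The case against.** Bleeding is not unmeasured. Clinically evident bleeding, transfusion and re-intervention all fall within a listed secondary outcome to 1 month. A reader might infer that the two-hour haemoglobin is the only measurement of bleeding. It is only the sole scheduled laboratory measure.

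A reader might also infer that the plan itself expects bleeding to continue past two hours. It does not say so. It sets a condition for tube removal, for patients with a tube, and discoloured effluent does not prove a material further fall in haemoglobin.

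A third tempting reading is that the bleeding benefit can be neither confirmed nor refuted. The illustrative power of 68–93% (75–96% with 320 per arm) does not support that, and the attenuation behind those figures is itself assumed.

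Nor does Table 1 contradict the text. The row is labelled as immediate postoperative labs and sits in the broad post-allocation column, as the 24-hour pain score does. That is labelling only.

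Finally, lower bleeding risk is a premise of the margin, and it is debatable whether every premise needs its own endpoint. Any bias would be conservative for FANS f-URS, and the primary inference does not move.

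All of this stands, and it limits the point to a minor one. What remains is that a benefit the article itself trades against stone-free rate has no named outcome, and that its one quantitative measure is taken early.

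**Conclusion.** The point holds as a minor improvement to a secondary safety measure. Two parts rest directly on the text: section 3.2 names no bleeding outcome although section 5.11 uses bleeding to defend the margin, and the only scheduled haemoglobin comparison is at two hours. Two parts are inference: that some blood loss comes later, and that it falls more in the mini-PCNL arm. Their size cannot be derived from the documents. If they hold, the trial would tend to understate the FANS advantage, not exaggerate it. The stone-free comparison, the 8.5-point margin and the 278 per group are unaffected.

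**What to change.** - In section 3.2, name change in haemoglobin as a secondary outcome and report transfusion (yes/no) alongside it.
- Analyse haemoglobin by ANCOVA on the preoperative value, in place of the unadjusted test in section 5.12. The preoperative value is already collected, so this is free. With similar variances before and after surgery and correlation ρ between the two samples, the variance is (1 + ρ)/2 times that of a plain comparison of changes, so it is no larger.
- Add one outcome blood count at the same fixed postoperative hour in both arms. The sponsor should choose an hour that falls before the earliest discharge the protocol permits. The postoperative CT is not a suitable anchor: it may fall anywhere within 72 hours, and FANS patients may already have left, so timing could differ between arms.
- Keep the two-hour sample as a safety check, and show both samples with their times in Table 1.

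The cost is one line in section 3.2, one in section 5.12, an edit to Table 1 and one extra blood count per patient, a small burden felt most by FANS patients who leave early. No extra participants are needed. The transfusion and discharge rules are not at issue and stay as they are.
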